## Abstract

**Background:**

Smoking among people with severe mental illness (SMI) is highly prevalent and strongly associated with poor physical health. Currently, evidence-based smoking cessation interventions are scarce and need to be integrated into current mental health care treatment guidelines and clinical practice. Therefore, the present study aims to evaluate the implementation and effectiveness of a smoking cessation intervention in comparison with usual care in people with SMI treated by Flexible Assertive Community Treatment (FACT) teams in the Netherlands.

**Methods:**

A pragmatic, cluster-randomised controlled trial with embedded process evaluation will be conducted. Randomisation will be performed at the level of FACT teams, which will be assigned to the KISMET intervention or a control group (care as usual). The intervention will include pharmacological treatment combined with behavioural counselling and peer support provided by trained mental health care professionals. The intervention was developed using a Delphi study, through which a consensus was reached on the core elements of the intervention. We aim to include a total of 318 people with SMI (aged 18–65 years) who smoke and desire to quit smoking. The primary outcome is smoking status, as verified by carbon monoxide measurements and self-report. The secondary outcomes are depression and anxiety, psychotic symptoms, physical fitness, cardiovascular risks, substance use, quality of life, and health-related self-efficacy at 12 months. Alongside the trial, a qualitative process evaluation will be conducted to evaluate the barriers to and facilitators of its implementation as well as the satisfaction and experiences of both patients and mental health care professionals.

**Discussion:**

The results of the KISMET trial will contribute to the evidence gap of effective smoking cessation interventions for people treated by FACT teams. Moreover, insights will be obtained regarding the implementation process of the intervention in current mental health care. The outcomes should advance the understanding of the interdependence of physical and mental health and the gradual integration of both within the mental health care system.

**Trial registration:**

Netherlands Trial Register, NTR9783. Registered on 18 October 2021.

## Introduction

Smoking is the leading cause of preventable morbidity and mortality. Among people with severe mental illness (SMI), such as psychotic disorders, smoking is highly prevalent and strongly associated with poor physical health [1, 2]. It is implicated in reducing the life expectancy of people with SMI by 15–25 years, primarily due to cardiovascular diseases, cancer, and respiratory diseases [2, 3]. Approximately 50–80% of people with SMI smoke, a rate approximately two to three times higher than that in the general population [4].

Compared with the general population without psychiatric disorders, people with SMI are a vulnerable group that is more prone to becoming addicted to substances such as tobacco [3, 5]. The increased likelihood of tobacco dependence among people with SMI can be explained by several mechanisms, such as genetic risk factors; for example, schizophrenia and smoking behaviour have been found to be related to several shared genetic loci [6, 7]. Another potential mechanism is socioeconomic status (SES), with people of a lower SES being more likely to have psychotic disorders [8] and to smoke [9] compared with people of a higher SES.

The self-medication hypothesis assumes that people with SMI use smoking to alleviate specific symptoms, such as depressed mood and cognitive problems. It is also assumed that smoking counterbalances the side effects of psychopharmaca [10]. However, no clear evidence exists to support these hypotheses, and the consequences of holding beliefs based on them are critical [11]. The assumptions of self-medication and symptom alleviation through smoking advance the notion that an individual’s mental health problems could worsen following smoking cessation; however, this has not been confirmed by existing research. Systematic reviews have demonstrated that mental health does not deteriorate and even improves moderately following smoking cessation [12, 13]. In addition to expecting unfavourable mental health outcomes, many mental health care professionals (MHCPs) lack confidence in the opportunities for their patients’ successful smoking cessation [14]. This not only impedes the collective process of rethinking smoking within mental health care but also has the potential to deprive people with SMI of appropriate support for smoking cessation.

In the treatment of psychiatric patients, the integration of physical and mental health care is a recently prioritised goal. This has led to the formation of a new body of research on ‘lifestyle psychiatry’ [15]. Systematic reviews have provided evidence that the promotion of a healthy lifestyle, including smoking cessation, has a positive impact on both physical and mental health outcomes for patients with SMI [16, 17]. However, while lifestyle interventions are increasingly being effectively and sustainably implemented within mental health care, a consensus exists that the rate remains rather low and should be improved [18].

In the Netherlands, new policy measures have recently been implemented to reduce tobacco use nationwide, including a smoking ban in all Dutch mental health institutions by 2025 [19]. Currently, most of these institutions do not offer sufficient support for smoking cessation, which is partly due to a lack of effective smoking interventions [20]. Research has demonstrated that behavioural support and pharmacotherapy are the most effective treatments for tobacco addiction. Two forms of behavioural support that are commonly used for people with and without SMI are motivational interviewing [21, 22] and cognitive behavioural therapy (CBT) [23, 24]. Combined CBT and pharmacotherapy treatment has been found to be more effective than CBT alone [24–26]. In terms of pharmacotherapy, the use of varenicline, bupropion, and nicotine replacement therapy have all been found to be safe and effective treatments for smoking cessation in people with SMI [27, 28]. Alongside CBT and pharmacotherapy, the addition of peer support can also be valuable in smoking cessation treatment. Several studies have indicated that it can strengthen individuals’ social network and social support [29], which can positively contribute to the success of smoking cessation [30, 31]. This is especially relevant for people with SMI, who tend to have limited social networks [32, 33].

In the Netherlands, people with SMI are predominantly treated by Flexible Assertive Community (FACT) teams. A FACT team consists of a multidisciplinary team of MHCPs who offer ambulatory care. Such teams aim to offer treatment for psychiatric disorders combined with support for personal, functional, and social recovery. Given the long-term support that they provide to patients with SMI, FACT teams have an excellent opportunity to deliver smoking cessation interventions to them. Currently, no evidence-based smoking cessation intervention has been studied in a Dutch mental health care setting. Therefore, this study aims to evaluate the implementation and effectiveness of a smoking cessation intervention compared with usual care in people with SMI treated by FACT teams in the Netherlands (KISMET). The remainder of this paper is organised as follows. The following section presents the methods that will be applied and includes the inclusion- and exclusion criteria, the contents of the intervention, primary and secondary study outcomes and a statistical analysis plan. The final section discusses the strengths and challenges of the study design as well as the authors’ motivation and contribution of the present study to the research field.

## Methods

### Design

The KISMET smoking cessation intervention will be evaluated in a pragmatic, cluster-randomised controlled trial (cluster-RCT) with a follow-up period of 1 year. Data will be collected at baseline and 3, 6, and 12 month follow-up. A qualitative process evaluation will be conducted alongside the trial.

### Setting

The intervention will be implemented within ambulatory mental health care teams in the Netherlands.

### Participants

Participants will be people with SMI who receive treatment from FACT teams. Patients who fulfil the following criteria will be eligible for inclusion:Fulfils the criteria of SMI according to Delespaul and the SMI Consensus Group, which are defined as follows [34]: presenting a non-transient (structural or long-term for several years) psychiatric disorder, for which coordinated care from a care network is necessary and which is not in symptomatic remission; presenting severely impaired social and/or occupational functioning which is not in functional remission;Aged ≥18 years;Current smoker (≥ 5 cigarettes) without a quit attempt in the past month;Expresses an interest in stopping / cutting down smoking;Willing and able to sign informed consent.

Patients who are pregnant or breastfeeding, have severe cognitive impairments, present a primary diagnosis of substance use disorder (with the exception of cannabis use disorder), or are experiencing an acute psychiatric crisis or acute physical disease at the time of inclusion will not be eligible to participate.

### Randomisation

Randomisation will be performed by institution at the FACT team level. Through this cluster-randomisation, contamination between the experimental and control groups can be avoided [35]. Before participants are included, the participating FACT teams will be randomly assigned to either the smoking cessation intervention (intervention group) or usual care (control group). The randomisation will be performed by an independent statistician, who is not involved in the execution of the study, using a computer-generated list of random numbers. Due to the nature of the intervention and the study design, the blinding of patients and FACT team members will not possible.

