### Recruitment

To recruit eligible patients, the teams will compose a list of possible participants receiving treatment from FACT teams. The coordinating MHCPs will evaluate whether each patient meets the inclusion and exclusion criteria. Eligible patients will be approached by the responsible MHCP and informed about the study, both orally and in writing. The patients will have a minimum of 1 week to decide whether to participate and sign the informed consent form. If a patient decides to participate, he or she will be provided with additional information about the study by the researchers. Figure 1 presents an overview of the study design and participants’ flow throughout the trial:

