### Usual care

FACT teams in the control condition will not receive any training and will provide usual care. Thus, people with SMI will have unrestricted access to mental health care and treatment for smoking cessation according to current national guidelines [37]. Furthermore, they will not be allowed to participate in a structured smoking cessation programme for the duration of the study. In case of positive outcomes of this intervention study, control group participants will be offered support to quit smoking in line with the KISMET intervention.

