### Training of MHCPs

The KISMET intervention will be provided by trained mental health care workers. Two MHCPs (mental health nurses, clinical nurse specialists, and experts-by-experience) from FACT teams assigned to the intervention condition will participate in a one-day training session. They will function as role models for their colleagues within the FACT team as well as their patients on the subject of smoking cessation and will guide the group sessions. The training will consist of the following: (a) education about pharmacological treatment for smoking cessation, including its effectiveness and possible side and interaction effects; (b) CBT techniques; (c) motivational interviewing techniques; (d) psychoeducation about the connection between SMI, mental health, and tobacco addiction; and (e) principles of peer support. Furthermore, information will be provided about the study design and measurement of the study parameters. The training will be set up and provided by three highly experienced trainers with ample expertise on smoking cessation and mental health. The FACT teams can decide which health care workers will be trained for the intervention. This will promote a greater resemblance to general care as well as enhance the generalisability of the study.

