##### Psychotic symptoms

We will assess the severity of psychotic symptoms using the six-item Positive and Negative Syndrome Scales (PANSS-6). The PANSS-6, a shorter version of the original 30-item PANSS, contains only six items and is therefore more feasible [45]. This version is a validated compilation of three negative symptoms (N1 – Blunted affect, N4 – Social withdrawal, and N6 – Lack of spontaneity and flow of conversation) and three positive symptoms (P1 – Delusions, P2 – Conceptual disorganisation, and P3 – Hallucinations). The PANSS-6 will be scored by the MHCP who knows the patient best.

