The recruitment during this trial might pose a challenge. First, recruiting mental health institutions and affiliated FACT teams is difficult, especially in light of the ongoing burden imposed by COVID-19 on the mental health sector and the nationwide introduction of a new funding system. Second, participating FACT teams might encounter difficulties with the inclusion of patients. Recruitment in mental health trials is a common challenge [65]. Therefore, a clear recruitment strategy is essential for including an adequate number of participants. Based on the outcomes of the SCIMITAR trial in similar settings [66], the most critical aspects for successful recruitment are the motivation of MHCPs to support patients in their efforts to quit smoking and their relationship with their patients [67]. A strong therapeutic alliance can positively affect quitting and maintaining abstinence, which is potentially explained by more mutual trust, closer collaboration, and the exchange of positive emotions. These characteristics of a strong therapeutic relationship can facilitate open communication about challenges and difficulties.

Alongside the RCT, we will also conduct a process evaluation at the patient and mental health care professional levels through in-depth interviews. The overall aim is to examine barriers, facilitators, experiences, and perspectives regarding implementation. This approach will combine both quantitative RCT outcomes with qualitative process evaluation outcomes, thereby increasing the internal validity of this study. Thus, we will gain a comprehensive understanding of the working mechanisms of this intervention’s implementation. This will aid in establishing recommendations for further developing the intervention and strategies for (more) effective implementation. Another objective of the process evaluation is to identify relevant aspects for future research as well as how to more effectively promote innovation within the mental health care sector.

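### Unblinded teams list, screen and approach patients, and the article describes no listing or screening before a team's allocation is revealed, so the arms may differ in unmeasured readiness to quit.

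*Protocol article*

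**What the plan says.** Under Randomisation, the protocol article sets the order: "Before participants are included, the participating FACT teams will be randomly assigned to either the smoking cessation intervention". An independent statistician does this from a computer-generated list. The same section says that "the blinding of patients and FACT team members will not possible".

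Under Recruitment, every step up to the patient's decision belongs to the teams: "the teams will compose a list of possible participants receiving treatment from FACT teams"; then "The coordinating MHCPs will evaluate whether each patient meets the inclusion and exclusion criteria"; then the responsible clinician approaches and informs the patient. Researchers add information only once the patient has decided to take part.

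Four other places bear on this:

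- **Participants:** one entry criterion is an expressed interest in stopping or cutting down.
- **Usual care:** control participants may not join a structured cessation programme during the study.
- **Discussion:** citing experience from an earlier trial in similar settings, the article says that "the most critical aspects for successful recruitment are the motivation of MHCPs to support patients in their efforts to quit smoking", together with the clinicians' relationship with their patients.
- **Statistical analysis:** the first model for the primary outcome contains treatment only. Further models adjust for prognostic variables, with precision as the stated aim.

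**The concern.** Randomising teams balances teams, in expectation. It does not balance the patients whom each team later enrols if the people choosing and approaching them know the arm.

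Three features of the plan make differential enrolment plausible. The interest criterion rests partly on the clinician's judgement and is likely to be prognostic. Clinician motivation, which the article itself ties to recruitment, may differ between teams about to deliver a new programme and teams asked to carry on as usual. Patients also weigh different offers when they consent, since only one arm has access to a structured programme.

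If enrolled patients differ in readiness to quit, part of the difference in abstinence at 12 months reflects who was enrolled rather than what they received. The baseline schedule in Table 1 includes nicotine dependence, smoking history and quit attempts, but lists no measure of motivation to quit. Adjustment can therefore reach this factor only indirectly.

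**Working it through.** **1. The plan's own figures.** Inputs from Sample size: 30% against 15% abstinence, 121 per group, ICC 0.05, 10 participants per team, 127 per arm after the clustering correction, 20% loss, 318 in total. Significance level and power are not stated; I assume two-sided 5% and 80%.

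n = [1.96 × √(2 × 0.225 × 0.775) + 0.842 × √(0.30 × 0.70 + 0.15 × 0.85)]² / 0.15² = (1.157 + 0.489)² / 0.0225 = 120.5, so 121. This matches. Also 127 / 0.8 = 158.75, so 159 per arm and 318 in total, which matches.

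**2. Effective size for the illustration.** Design effect = 1 + (10 − 1) × 0.05 = 1.45. With 127 analysed per arm, the effective number is 127 / 1.45 = 87.6.

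**3. False-positive rate if selection alone shifts the intervention arm.** The shifts are my assumptions; there is no true effect and the control rate is 15%. SE = √[(p₁(1 − p₁) + 0.15 × 0.85) / 87.6], and the rejection rate is Φ(d/SE − 1.96) + Φ(−d/SE − 1.96).

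| Intervention rate | Spurious difference d | SE | d/SE | Rejection rate |
|---|---|---|---|---|
| 17% | 2 points | 0.0554 | 0.36 | 6.5% |
| 20% | 5 points | 0.0573 | 0.87 | 14% |
| 25% | 10 points (extreme) | 0.0600 | 1.67 | about 38% |

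**4. What imbalance these shifts need.** Suppose ready patients quit at 30% and others at 10% (assumed). The arm's rate is 0.10 + 0.20 × (share ready), so a 15% control rate means 25% ready. A rate of 17% needs 35% ready, 20% needs 50%, and 25% needs 75%. The imbalances are 10, 25 and 50 percentage points.

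**5. Opposite direction.** Suppose the true rates are 30% and 15%, and selection lowers the intervention arm. Power is Φ(d/SE − 1.96) at 87.6 effective per arm:

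- no selection: d/SE = 0.15/0.0621 = 2.42, power about 68%
- 2 points lost: 0.13/0.0613 = 2.12, power about 56%
- 5 points lost: 0.10/0.0600 = 1.67, power about 38%

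**6. Dependence on the design effect.** With 121 effective per arm, the plan's own pre-clustering number, the 2-, 5- and 10-point shifts give rejection rates of about 7%, 18% and 50%. The point does not depend on disputing the plan's clustering correction.

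**The case against.** The best objection is that the article never says teams list patients after learning their arm. It says that assignment precedes inclusion, not when teams are told or when the list is drawn up, and the participant flow figure is not available. A reader might infer that allocation is certainly known at listing; the text does not establish that. What stands is narrower: recruiters are unblinded, randomisation comes first, and no stated step protects listing or screening.

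A reader might also infer that the bias must favour the intervention. It need not. The Discussion links clinician motivation to successful recruitment, not to enrolling better quitters. Keen teams could enrol less-ready patients, and the criterion admits those who only want to cut down. Control participants are also promised support later if results are positive, which softens the disincentive to consent.

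Existing safeguards count for something. The independent statistician protects team allocation. Baseline dependence, smoking history and quit attempts are recorded, and prognostic adjustment guided by causal diagrams is planned. These deal with measured differences only.

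Finally, a reader might infer from "information will be provided about the study design and measurement of the study parameters", set beside "FACT teams in the control condition will not receive any training and will provide usual care", that only intervention-arm clinicians are told how to score the PANSS-6. The documents do not support this. The first describes what the intervention training contains. The second can be read as training in the intervention, and a separate measurement briefing for control teams is not ruled out.

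**Conclusion.** The concern holds as a risk that the plan leaves open and could cheaply reduce. Followed as written, it lets unblinded clinicians select and approach patients on a criterion that is plausibly prognostic. Neither the treatment-only model nor adjustment for measured variables can fully repair the result.

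Size and direction cannot be determined from the article. Under the assumed shifts of 2 to 5 points, the false-positive rate rises from 5% to about 6.5% to 14%; selection the other way costs power. The 38% figure needs a 50-point imbalance in readiness under the model shown, so it is an extreme case and not an expectation. These figures assume a two-sided 5% test, 127 analysed per arm and a design effect of 1.45. The change is advisable; the material does not show that the comparison is invalid.

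**What to change.** Have each team compile and screen its list of eligible patients and lock it before the independent statistician releases that team's allocation. Require the team to approach every patient on the locked list. Report the numbers listed, eligible, approached and consenting by arm, so that readers can judge any differential recruitment. If the full protocol already has such a step, one sentence in the article would settle the point.

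Obtain consent and baseline measures before release only where feasible. Patients have at least a week to decide, and baseline includes fasting blood tests and a walk test, so this adds real delay in a trial that already expects recruitment difficulty. Where consent follows release it remains unblinded, and locking the list reduces the problem without removing it.

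The basic change reorders steps the teams already perform. Its cost is a short wait before teams learn their arm, plus keeping the counts.

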### Recruitment

To recruit eligible patients, the teams will compose a list of possible participants receiving treatment from FACT teams. The coordinating MHCPs will evaluate whether each patient meets the inclusion and exclusion criteria. Eligible patients will be approached by the responsible MHCP and informed about the study, both orally and in writing. The patients will have a minimum of 1 week to decide whether to participate and sign the informed consent form. If a patient decides to participate, he or she will be provided with additional information about the study by the researchers. Figure 1 presents an overview of the study design and participants’ flow throughout the trial:

